**Methods and analysis:**

The REPLACE study is a multicentre, non-inferiority- randomized controlled trial designed to assess whether retaining the urinary catheter in patients with CAUTI is non-inferior to replacement in terms of the risk of a recurrent CAUTI within 90 days. Secondary outcome measures include 30-day mortality, health-related quality of life, time to resolution of CAUTI symptoms, complications related to catheter replacement and healthcare and societal costs. Patients aged 18 years or older with an indwelling catheter (transurethral or suprapubic) and CAUTI are eligible. CAUTI is defined according to the Infectious Diseases Society of America (IDSA) criteria. Three hundred patient will be randomised 1:1 to catheter retention (intervention group) or replacement (control group). In the intervention group, the catheter is not replaced. In the control group the catheter will be replaced within 3 days after start of antibiotic therapy. The primary outcome (recurrent CAUTI within 90 days) will be assessed for non-inferiority (margin of 10%).

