#### Exclusion criteria

A potential participant who meets any of the following criteria will be excluded from participation in this study:

Antibiotic treatment initiated more than 3 days prior to inclusion.Immunodeficiency: High-dose corticosteroid use (any equivalent of ≥ 20 mg prednisolone per day for > 4 weeks), severe primary immunodeficiency, organ transplant, neutropenia (absolute neutrophil count < 0.50 × 10⁹/L).Discontinuation of the indication for the indwelling catheter.A planned (routine) catheter replacement during antibiotic therapy.Contraindications for catheter replacement.Kidney catheters (nephrostomy or double-J catheter).Needing continuous bladder irrigations because of gross haematuria.Bladder stones.Pregnancy.A life expectancy of less than 90 days, as estimated by the treating physician.

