### Study interventions

Patients will be assessed for CAUTI according to standard practice of care. Potential participants will be screened against inclusion/exclusion criteria by the central study team. Eligible patients will receive written study information and provide written or remote informed consent before randomization.

After obtaining informed consent, participants will be randomized to either catheter replacement (control group) or catheter retention (intervention group). In the replacement group, the catheter will be replaced within 3 days of starting antibiotic treatment. All patients (men and women) will receive a 10-day course of antibiotics. The choice of antibiotic agent is at the discretion of the treating physician, except for nitrofurantoin, fosfomycin, and trimethoprim as these may be considered inferior for the treatment of CAUTI with systemic symptoms. Once culture and susceptibility results are available, therapy must be adjusted according to the EUCAST susceptibility criteria.

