### Outcome measures

The primary outcome is a recurrent CAUTI within 90 days after completion of antibiotic treatment, defined according to the same IDSA-based clinical and microbiological criteria used for inclusion. The pathogen does not have to be identical to the causative pathogen that was identified during the first episode.

All participants are instructed to contact the central study team should they experience CAUTI symptoms. Additionally, the physicians at the participating centres and general practitioners are instructed to report potential recurrences among participants.

Secondary outcomes:

Patient-related outcomes: 30-day mortality, health-related quality of life assessed using the PROMIS and EQ-5D-5L questionnaires.Process-related outcomes: time to resolution of CAUTI symptoms, time to resolution of fever, complications of catheter replacement and severity of the complications (5-level Likert scale).Resource-related outcomes: length of hospital stay, ICU-admission during hospital stay, healthcare and societal cost using a selection of items relevant for this population of the medical consumption (iMCQ) and productivity (iPCQ) questionnaire.

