#### Analyses of outcome measures

Descriptive statistics will be used to summarize baseline characteristics. In the primary analysis, the risk difference with (two-sided) 95% confidence interval will be computed to compare the differences in 90-day recurrence risk between the two treatment arms, in both the intention-to-treat population and the per-protocol population. Regarding the primary analysis, multiple imputation will be used to deal with missing outcome data (i.e. missing information regarding CAUTI recurrence). For the primary outcome, three sensitivity analyses will be performed to account for missing data. In the first sensitivity analysis, a complete case analysis will be performed. Additionally, a worst-case and best-case scenario analysis will be performed, in which patients who drop out of the study before 90 days will be included under the assumption that they experienced a recurrence (worst-case scenario) or no recurrence (best-case scenario), respectively.

The primary analysis will not take patient characteristics into account, as these are expected to be balanced between treatment groups (by randomization). In a secondary analysis, multivariable analysis will be performed including variables that are associated with recurrence of CAUTI.

The secondary outcome time-to-resolution will be analysed using Kaplan Meier survival analysis. For patient-related outcomes measures, such as PROMIS and EQ-5D-5 L, repeated measures analyses will be performed to compare these outcomes between the groups. For these outcome measures, multiple imputation will be used to deal with missing outcome data. Process and resource related outcome measures will be analysed in the per-protocol population. In addition, a cost-effectiveness analysis from a societal perspective with a 6-month time horizon and a budget impact analysis will be performed.

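### Process and resource outcomes are assigned to the per-protocol population alone, so these between-arm comparisons lose the protection of randomisation and can be biased, probably but not certainly toward retention

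*Protocol article*

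**What the plan says.** Under Analyses of outcome measures, the protocol article states that "Process and resource related outcome measures will be analysed in the per-protocol population". The Outcome measures section shows what this covers. The process group is "time to resolution of CAUTI symptoms, time to resolution of fever, complications of catheter replacement and severity of the complications". The resource group includes "length of hospital stay, ICU-admission during hospital stay, healthcare and societal cost". Of the listed secondary outcomes, only 30-day mortality and quality of life fall outside the sentence.

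The primary outcome is treated differently: its risk difference is estimated "in both the intention-to-treat population and the per-protocol population". No reason is given for using per-protocol alone elsewhere. The article also plans "a cost-effectiveness analysis from a societal perspective with a 6-month time horizon" and a budget impact analysis, without naming a population for either.

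Assigned treatment is described in the abstract for retention ("In the intervention group, the catheter is not replaced") and under Study interventions for control ("In the replacement group, the catheter will be replaced within 3 days of starting antibiotic treatment"). The article does not define the per-protocol population.

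**The concern.** A per-protocol set is chosen on what happens after randomisation. Here the relevant event is a catheter change, or the absence of one, and clinicians and patients know the allocation. The exclusion criteria remove patients with "A planned (routine) catheter replacement during antibiotic therapy", so a change in the retention arm during therapy would mostly be unplanned and could follow a poor course. If such patients leave the set, the remaining retention arm looks healthier than the arm that was randomised. In the control arm, a patient who recovers or goes home before the change may leave as well, and so may one who is too unwell for it.

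Per-protocol analysis is usually given weight in a non-inferiority comparison because intention-to-treat can blur a real difference. That argument does not carry over: the only margin stated is for recurrence. The protocol itself relies on randomisation for balance when it leaves its primary analysis unadjusted, and a per-protocol comparison alone gives that up.

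At stake are the statements on speed of recovery, hospital stay, ICU use and cost. The Discussion expects lower cost and patient burden if retention succeeds, and these outcomes would have to support much of that.

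**Working it through.** **Plan's own figure.** The disputed sentence carries no number. The nearby sample size statement (150 per arm, 10% recurrence in both arms, margin 10%, one-sided 2.5%, power about 80%) reproduces: 80.3% with a Newcombe interval and 78.8% with the Farrington-Manning score test. It concerns the primary outcome and is not affected.

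**Assumed inputs (the article gives none).** The two arms have identical true outcomes. Time to resolution is log-normal with median 4 days and log-SD 0.6. Stay is log-normal with median 5 days and log-SD 0.7. ICU admission is 5%. A latent severity has correlation 0.7 with each outcome (on the log or latent scale) and 0.7 with the tendency to deviate, so outcome and deviation correlate at ρ = 0.7 × 0.7 = 0.49. A fraction f of the arm leaves the set.

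**Formula.** Full-arm mean: M = median × exp(σ²/2). Mean among those kept: M × Φ(z − ρσ)/(1 − f), where z is the (1 − f) normal quantile.

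- Time to resolution: M = 4 × exp(0.18) = 4.79 days. At f = 10%: Φ(1.282 − 0.294) = 0.838, and 4.79 × 0.838/0.90 = 4.46, a shift of −0.33 days.
- Stay: M = 5 × exp(0.245) = 6.39 days. At f = 10%: Φ(1.282 − 0.343) = 0.826, and 6.39 × 0.826/0.90 = 5.86, a shift of −0.53 days.

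**Only retention deviations related to severity** (control deviations absent or unrelated to it). Differences are retention minus replacement; the true value is 0.

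| Retention patients leaving | Mean time to resolution | Mean stay | ICU, retention v control |
|---|---|---|---|
| 5% | −0.19 days | −0.31 days | 4.0% v 5.0% |
| 10% | −0.33 days | −0.53 days | 3.4% v 5.0% |
| 20% | −0.55 days | −0.87 days | 2.7% v 5.0% |

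**Control deviations also related to severity** (difference in mean time to resolution):

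| Retention leaving | 10% of control, sicker | 20% of control, sicker | 10% of control, healthier |
|---|---|---|---|
| 5% | +0.13 | +0.36 | −0.42 |
| 10% | 0.00 | +0.22 | −0.55 |
| 20% | −0.22 | 0.00 | −0.78 |

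The sign therefore depends on who deviates in the control arm. A simulation with 1,000,000 patients per arm agrees with these values to within about 0.01 days, and its intention-to-treat differences are about 0 throughout.

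**Upper bound at 10%.** Set ρ = 1, so that exactly the slowest 10% of one arm are removed. Time to resolution: 4.79 × 0.752/0.90 = 4.00, a shift of about −0.8 days. Stay with a wider log-SD of 0.8: M = 5 × exp(0.32) = 6.89, and 6.89 × 0.685/0.90 = 5.24, a shift of about −1.6 days. With log-SD 0.7 the stay figure is about −1.3 days.

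**Medians.** The plan uses Kaplan-Meier for time to resolution, so the median matters too. At 10% it moves from 4.0 to 3.8 days with ρ = 0.49, and to 3.7 days at the upper bound.

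**The case against.** The case on the other side has several parts.

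- **Direction.** A reader might infer that the rule favours retention as a settled matter. The article gives no per-protocol definition, deviation rate or reason for deviating, and it does not say that an unplanned change removes a retention patient from the set. The calculation shows cancellation or reversal when sicker control patients deviate. This part stands: toward retention is the likelier direction, no more. An unknown sign is still bias and does not rescue per-protocol alone.
- **Size.** The upper-bound figures suppose that deviation is fully determined by outcome in one arm only. They are not a forecast.
- **Economic evaluation.** A reader might infer that the cost-effectiveness ratio will combine per-protocol costs with EQ-5D from all randomised patients. The article names no population for that analysis or for quality of life, so this is a risk if the sentence is followed literally for costs, not a stated plan.
- **Complications.** These arise only when a catheter is changed, so a description by procedure received is reasonable. The direction of bias is also unclear here: per-protocol could drop late changes in the retention arm, but also failed or delayed ones in the control arm.
- **Condensed article.** The definition of the set may properly sit in the full protocol or SAP. That does not answer the point, because the choice of population is stated here and a SAP that follows it carries it forward.

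**Conclusion.** The point holds as a stated analysis choice that should be changed. The listed process and resource outcomes have no named intention-to-treat analysis, and their per-protocol comparison can be biased by post-randomisation selection, probably but not certainly toward retention.

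Under the assumed rates of 5% to 20%, with control deviations absent or unrelated to severity, the spurious difference is about 0.2 to 0.6 days in mean time to resolution and 0.3 to 0.9 days in mean stay. At 10%, the bound is about 0.8 and 1.6 days. These sizes rest wholly on assumed distributions, severity links and deviation rates.

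A reader might also infer that the trial's main result is compromised. It is not: recurrence is analysed in both populations, and the Discussion ties standardising practice to non-inferiority being shown. Only secondary outcomes are affected.

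**What to change.** - Make intention-to-treat, defined as for the primary outcome, the main analysis for time to symptom and fever resolution, length of stay, ICU admission, and healthcare and societal costs. Keep per-protocol as supportive.
- Name that same intention-to-treat population for both costs and effects in the cost-effectiveness analysis.
- Report complications of catheter replacement and their severity by randomised arm, counting every catheter change in either arm, and separately by procedure received.

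The cost is mainly a change of wording in the protocol and SAP; sample size, power and alpha do not change. The article plans 180 days of follow-up without limiting it to adherent patients, so most of the data should exist. It does not say whether patients excluded after randomisation on the culture criterion are still followed. The sponsor should confirm this, and also that catheter changes are recorded in both arms.

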## Abstract

**Background:**

Catheter-associated urinary tract infection (CAUTI) is the most common healthcare associated infection. Current guidelines state that catheters should be replaced in patients with CAUTI to hasten symptom resolution and to lower the risk of recurrence. However, the available literature is limited and there is significant practice variation globally. The aim of this study is to determine whether not changing the catheter during CAUTI treatment affects the recurrence-risk.

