## Background

Due to the widespread use of urinary catheters, catheter-associated urinary tract infection (CAUTI) is the most common healthcare-associated infection [1]. As urinary catheter use is expected to rise with an aging population, the number of CAUTIs will likely increase accordingly [2]. CAUTIs can result in serious, sometimes fatal complications, including urosepsis [3–6].

To fasten recovery and reduce the risk of recurrent CAUTI, current guidelines recommend to replace the catheter at the onset of CAUTI when the indwelling catheter has been in place for more than two weeks [1, 6, 7]. This recommendation, however, is based on limited evidence as only four conflicting studies have been identified that investigate catheter replacement during CAUTI [8]. Current guidelines rely on only one of these four studies which is a small randomized controlled trial (RCT) that favoured catheter replacement [9]. The study reported shorter recovery times and lower recurrence rates in the replacement group compared to the retention group. These findings were contradicted by a second RCT [10], which found higher recurrence rates in the replacement group. However, in that study, antimicrobial treatment was shorter in the replacement group. Two observational studies found no effect of catheter replacement on either recurrence or symptom duration [11, 12], highlighting the paucity of the current state of evidence on catheter management during CAUTI.

In light of the limited evidence, a survey has been conducted to assess clinical practice regarding catheter management in CAUTI (manuscript in preparation [13]). It revealed considerable variation in catheter management practices among urologists, microbiologists, and internists. Urologists indicated more often that they routinely retain the transurethral catheter, compared to internists and medical microbiologists. The primary reasons for catheter replacement were the fact that it is a guideline recommendation and the expectation that replacement would be beneficial from a pathophysiological rationale. From a theoretical perspective, catheter replacement aligns with the principle of source control, as removal of the catheter may eliminate biofilm-associated pathogens that can persist during antimicrobial therapy and contribute to recurrent CAUTI [14]. Main reasons for retaining the catheter were the lack of scientific evidence supporting clinical benefit and the risk of procedural complications of the procedure.

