### Implications and future directions

Current national and international guidelines, advice to change the catheter with a low level of evidence [1, 7, 8]. If this trial demonstrate that catheter retention is non-inferior to replacement, clinical practice could be standardized accordingly in future guideline updates. This may reduce the number of invasive procedures, decrease healthcare costs, lower material waste and alleviate patient burden without compromising safety. Conversely, if catheter retention is not found to be non-inferior, the results will strengthen the evidence base supporting current recommendations for catheter replacement and may improve adherence in clinical practice.

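### Time to resolution, length of stay, ICU admission and costs are assigned to the per-protocol population with no intention-to-treat analysis stated, although recurrence gets both

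*Protocol article*

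**What the plan says.** Under Analyses of outcome measures, the 90-day recurrence risk is compared "in both the intention-to-treat population and the per-protocol population". Later in the same section one set only is named for two groups of secondary outcomes: "Process and resource related outcome measures will be analysed in the per-protocol population". The sentence giving Kaplan-Meier as the method for time to resolution names no other population.

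The section Outcome measures says what belongs to those groups. One is "Process-related outcomes: time to resolution of CAUTI symptoms, time to resolution of fever", together with complications of replacement and their severity. The other is "Resource-related outcomes: length of hospital stay, ICU-admission during hospital stay, healthcare and societal cost".

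Two analyses stand apart. The cost-effectiveness and budget impact analyses are added after the per-protocol sentence without a stated population. The patient-related outcomes (30-day mortality, PROMIS, EQ-5D-5L) are not placed under the per-protocol rule.

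**The concern.** Time to resolution bears directly on one of the two guideline reasons for changing the catheter. The Abstract reports the guideline position that "catheters should be replaced in patients with CAUTI to hasten symptom resolution and to lower the risk of recurrence". Of the small RCT on which the guidelines rely, the Background says: "The study reported shorter recovery times and lower recurrence rates in the replacement group compared to the retention group". Recurrence is therefore tested in both populations, while recovery is assigned to per-protocol alone.

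Per-protocol membership is decided after randomisation, and here it can depend on the outcome. Neither patients nor clinicians are blinded, guidelines favour replacement, and the article itself expects prior preferences. A retention patient who is not improving is a natural candidate for a catheter change. On the other side, "In the replacement group, the catheter will be replaced within 3 days of starting antibiotic treatment", so a control can leave the set by missing that window.

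Under Implications and future directions, a non-inferior result would support standardising retention so as to "decrease healthcare costs, lower material waste and alleviate patient burden without compromising safety". Slower recovery, longer stay, more ICU use or higher cost with retention would count against that, so these outcomes should also be compared in the groups as randomised.

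**Working it through.** **The plan's own figure.** The article gives no resolution, rescue or non-adherence rates. Its only related figure is the power for recurrence: Φ(0.10/√(2 × 0.10 × 0.90/150) − 1.96) = Φ(2.887 − 1.96) = 82%, consistent with the stated value of about 80%. It is not in dispute and the point does not depend on it.

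**Inputs for an illustration.** From the article: 150 per arm; a Day 8 visit; a 14-day symptom diary (follow-up censored at Day 14). Assumed: 15% unresolved at Day 8 with retention and 10% with replacement; exponential resolution; a share x of the retention arm changed for non-response (rescued) and then excluded from per-protocol.

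**Extreme case: every rescued patient would have been unresolved at Day 8.** Per-protocol retention = (0.15 − x)/(1 − x).
- x = 0.05: 0.10/0.95 = 10.5%, against 10% in controls.
- x = 0.03: 0.12/0.97 = 12.4%, against 10%.

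**Milder case: rescue at Day 5, control-arm resolution rate afterwards.**
- Daily rates: control −ln(0.10)/8 = 0.288; retention −ln(0.15)/8 = 0.237.
- Retention patients unresolved at Day 5: exp(−5 × 0.237) = 0.306. Fraction of these rescued: f = x/0.306, which is 0.164 for x = 0.05 and 0.098 for x = 0.03.
- Intention-to-treat at Day 8 = 0.15(1 − f) + x·exp(−3 × 0.288): 14.7% (x = 0.05), 14.8% (x = 0.03).
- Per-protocol at Day 8 = 0.15(1 − f)/(1 − x): 13.2% and 13.9%.

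The assumed 5-point gap therefore reads as 4.7 to 4.8 points by intention-to-treat and 3.2 to 3.9 by per-protocol; in the extreme case per-protocol shows 0.5 to 2.4.

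**Chance that a log-rank test shows slower resolution with retention** (simulated milder case, two-sided 5%; repeated runs differ by a point or two):

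| Rescued (retention) | Replacement missed (control) | Intention-to-treat | Per-protocol |
|---|---|---|---|
| 5% | none | 35–37% | 18–19% |
| 3% | none | 37–38% | 26% |
| 1% | none | 37% | 33–34% |
| none | 15% | 28% | 35% |
| 1% | 15% | 29% | 32% |
| 3% | 15% | 27% | 24% |

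In the last three rows, controls who miss replacement resolve at the retention rate and leave the per-protocol set.

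**No true difference.** With equal rates, per-protocol shows retention significantly faster in 9–11% of trials (5% rescued) or about 6% (3% rescued), against a nominal 2.5%. A second set of assumptions (median 4 days; 10–40% of retention patients still symptomatic at Day 3 or Day 5 changed and excluded, which is 4–24% of the arm) moves a true rate ratio of 1.00 to 1.04–1.22 in favour of retention.

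**Exclusions of controls.** If 5% of controls are excluded and all resolved early, the control arm reads 0.10/0.95 = 10.5% and the gap narrows. If all were unresolved at Day 8, it reads 0.05/0.95 = 5.3% and the bias runs against retention.

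**The case against.** The strongest reply is that the mechanism is assumed. The article does not describe a rescue change, give its frequency, or say that such a patient leaves the per-protocol set. That definition may properly sit in the full protocol or analysis plan. If a clinically indicated change is not a deviation, the modelled bias vanishes; with 1% rescued it is small. Intention-to-treat has its own weakness: the Background reports that urologists more often routinely retain the transurethral catheter, so missed replacements are plausible, and these dilute a true difference. That is a recognised reason to look at per-protocol when the question is whether omitting a procedure does harm. All of this stands. It argues for showing both sets; it does not justify naming per-protocol alone.

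A reader might also infer three stronger things, none of which the article supports:
- That these outcomes have no randomised comparison at all. Per-protocol still compares the randomised arms, after exclusions.
- That the whole economic evaluation is per-protocol. Only costs as a resource outcome are; the population for the cost-effectiveness and budget impact analyses is not stated and could be intention-to-treat.
- That the safety conclusion would rest on per-protocol alone. Recurrence is analysed in both sets, and mortality and quality of life are not limited to per-protocol.

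Finally, these are secondary outcomes without a stated margin or success rule, and in the illustration even intention-to-treat detects a 5-point gap in well under half of trials. The change would not settle the recovery question.

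**Conclusion.** The point holds as a stated choice of population that should be changed. Time to resolution of symptoms and fever, length of stay, ICU admission and costs are assigned to per-protocol with no intention-to-treat analysis named, in an open-label trial where leaving the per-protocol set can depend on recovery.

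It would be tempting to say that the rule necessarily flatters retention. The article does not support that: removal of slow resolvers from the retention arm favours retention, but exclusion of slow-resolving controls does the opposite. Under the assumed rates, the effect ranges from roughly halving the chance of seeing slower recovery (5% rescued), through almost nothing (1% rescued), to a modest advantage for per-protocol (15% of controls missing replacement and little or no rescue). Direction and size rest on adherence and on a per-protocol definition that the article does not give. The recurrence endpoint, its 10-point margin and its two analysis sets are not in question.

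**What to change.** State that time to resolution of symptoms and of fever, length of stay, ICU admission and costs are analysed in the same intention-to-treat population as the primary outcome as the main analysis, with per-protocol alongside as supportive. Report by arm the unplanned catheter changes during treatment, with the reason, and the replacements missed or made after the 3-day window. Leave complications of replacement as planned, since they concern patients who have one.

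The cost is about one sentence in the analysis section and one extra column per table. Symptoms, diary, length of stay and ICU admission are already collected; an item for the reason for a catheter change is needed only if the case report form lacks one. The sample size (300, with 400 randomised) does not change, and with recruitment planned to February 2028 the change can be made before the final analysis.

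The downside is that intention-to-treat compares assigned strategies, not pure retention with pure replacement, and is diluted by effective rescue (4.7 instead of 5.0 points in the illustration) or by missed replacements. That is why per-protocol stays alongside.
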